**Figure 2. F2:**
[figure not shown]
Unscheduled procedures flow chart.

The proportion of participants developing adverse events within 7 days of vaccination and serious adverse events within 6 months of vaccination will be identified through both active follow-up contacts (telephone and in person) and self-reporting by participants.

An immunogenicity sub-study will investigate the immune response to the vaccine by drawing blood 4 times throughout the study: on Day 0, on Day 28, at 18 months, and at 2 years post-vaccination. These blood samples will also be used to investigate the duration and persistence of IgG Vi-antibodies, using enzyme-linked immunosorbent assay (ELISA) vacyme, over time.

### Outcomes

The primary outcome is the incidence of blood culture–confirmed typhoid fever.

Other secondary and exploratory outcomes include: inpatient/outpatient admission rates for fever; rates of hospitalization for febrile illnesses; paratyphoid infection rates; lengths of hospital stays due to febrile illnesses; antibiotic use; durations of febrile illnesses; rates of all-cause hospitalizations; children’s growth in height and weight (measured at the beginning and end of the study for children under 5 years at the time of enrollment); rates of absenteeism from school/work as the result of illnesses; rates of all-cause mortality; rates of acute abdominal presentations; and surgical interventions. These outcomes will be measured via passive surveillance, participant follow-up interviews, and hospital record reviews.

Blood samples, collected from suspected typhoid cases and from the immunogenicity sub-study, will be analyzed to investigate individual host’s genetic susceptibility to typhoid, genetic control of immunity to the vaccine, and susceptibility to infectious diseases like typhoid, in those with and without Vi-TCV. Blood samples will have DNA extracted, and the DNA will be whole-genome genotyped using Illumina genotyping arrays. Genome-wide data will be used for a quantitative trait locus analysis, to identify those genes that contribute to the Vi antibody.

### Sample Size

The study is powered for the primary endpoint. Sample size calculations are based on the following assumptions (Table 2):

**Table 2. T2:** Sample Sizes Under Varying Assumptions in Nepal (80% Power, 5% Alpha)

Overall Incidence in the Entire Population Without Vaccination per 100 000	Direct Effect of Vaccine	Total Number to Enroll
100 cases py	80%	12 475
85 cases py	80%	14 677
100 cases py	75%	14 785
85 cases py	75%	17 395

Abbreviation: py, person-years.

An overall incidence of typhoid fever, in the absence of vaccination, of 85 cases per 100 000 people in the population per year, with 238 cases per 100 000 people per year in children under 16 years.Age-specific incidence rates were determined from the age distribution of typhoid cases, which is specific to Kathmandu, from published estimates and from site-specific surveillance data.A direct effect of vaccination of 75% and an indirect effect of 25%, based on mathematical modelling.A 25% loss to follow-up per year, due to participants moving out of the area.

These assumptions are conservative; however, to allow for further variation in the assumptions, the total sample size has been increased to 20 000 children (10 000 in each vaccination arm).

Over the 2-year follow-up of the trial, if the assumptions are correct, approximately 36 cases of typhoid in the control arm and 9 cases in the Vi-TCV arm are expected to be seen.

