### Intervention and Randomization

Vi-TCV will be the intervention vaccine, and a Meningococcal serogroup A vaccine (MenAfriVac) against *Neisseria meningitidis* serogroup A (MenA), manufactured by the Serum Institute of India, will be the control vaccine.

Participants will be randomized in a 1:1 ratio to receive either the Vi-TCV or MenA vaccine, using stratified block randomization with randomly varying block sizes from 6–12. Stratification will be by age (9 months to <5 years old or ≥5 years old to <16 years). Participant randomization will occur at the vaccination visit, using a purpose-built, offline, mobile application. Individual logins will be given to unblinded staff, which will allow secure access to the application. No trial staff will be able to make changes to randomization information stored on the application.

In addition, for those who consent to blood collection, the same mobile application will be used to randomly select 1500 individuals to be included in an immunogenicity sub-study. Blood sampling randomization will be on a 2:1 basis (1000 Vi-TCV and 500 MenA) and be age stratified (<5 years and ≥5 years). A diagram of planned trial activities can be seen in Figure 1.

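### The expected 36 control and 9 Vi-TCV cases do not follow from the listed assumptions; applying all of them gives about 27 and 7

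*Protocol article*

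**What the plan says.** The Sample Size section of the protocol article lists the inputs and presents both Table 2 and the case forecast as resting on them:

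- Incidence at all ages: "An overall incidence of typhoid fever, in the absence of vaccination, of 85 cases per 100 000 people in the population per year".
- Incidence in the age group enrolled, which is the rate that drives the forecast: 238 per 100 000 per year in those under 16.
- Vaccine effect: "A direct effect of vaccination of 75% and an indirect effect of 25%, based on mathematical modelling".
- Attrition assumed for the forecast and the table alike: "25% loss to follow-up per year, due to participants moving out of the area".

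For this base case Table 2 gives a total of 17 395 at 80% power and 5% alpha. The section then raises enrolment to 20 000, split equally between the arms, as a margin against departures from these inputs. It closes with the forecast, conditional on the assumptions being right, that "approximately 36 cases of typhoid in the control arm and 9 cases in the Vi-TCV arm are expected to be seen".

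The Data Analysis Plan section defines incidence as cases over person-years. It censors each participant at last known residence in or near the area, at last contact, or at the two-year visit. Children who leave therefore count until they leave.

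**The concern.** The forecast is offered as a consequence of the listed assumptions, so it should be recoverable from them. Two of them, the indirect effect and the annual loss, each lower the expected count by about a quarter. The printed figure has room for only one.

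This is the only event expectation in the article. Efficacy is one minus the incidence rate ratio, so the number of cases sets both the power and the width of the interval. A reader who takes 45 cases at face value will think the trial more informative than its own assumptions make it. The same reader will overestimate what is left for the planned age and sex subgroups.

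**Working it through.** **Inputs.** All are from the Sample Size section except the 1:1 allocation, which is from Intervention and Randomization: 10 000 per arm; child incidence 0.00238 per year; indirect effect 25% (factor 0.75); direct effect 75% (rate ratio 0.25); loss 25% per year, so 0.75² = 0.5625 retained at two years; follow-up 2 years.

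**Formula.** Control cases = 10 000 × 0.00238 × (person-years per child) × (indirect factor). Vi-TCV cases = control cases × 0.25. The indirect effect is applied to both arms.

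**Reproducing 36 and 9.**

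- Indirect effect kept, loss ignored: 10 000 × 0.00238 × 2 × 0.75 = 35.7 control; × 0.25 = 8.9 Vi-TCV.
- Loss kept at a constant rate, indirect effect ignored: person-years per child = (1 − 0.5625)/(−ln 0.75) = 0.4375/0.2877 = 1.521. Then 10 000 × 0.00238 × 1.521 = 36.2 control; × 0.25 = 9.0 Vi-TCV.
- Indirect effect in the Vi-TCV arm only, loss kept: 36.2 control and 36.2 × 0.75 × 0.25 = 6.8 Vi-TCV. This does not give 9.

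**Applying everything.** 10 000 × 0.00238 × 0.75 = 17.85 control cases for each person-year per child.

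| Timing of loss | Person-years per child | Control | Vi-TCV |
|---|---|---|---|
| End of each year | 1 + 0.75 = 1.75 | 31.2 | 7.8 |
| Middle of each year | 1.531 | 27.3 | 6.8 |
| Constant rate | 1.521 | 27.1 | 6.8 |
| Start of each year | 0.75 + 0.5625 = 1.3125 | 23.4 | 5.9 |

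With the indirect effect included, 36 control cases would need 36/17.85 = 2.02 person-years per child. That is the whole two-year follow-up with no loss.

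**Table 2 as a cross-check.** Take the two-rate formula: person-years per arm = (1.96 + 0.84)² × (λ₁ + λ₂)/(λ₁ − λ₂)², where the squared term is 7.849 before rounding. For the base row λ₁ = 0.00238 × 0.75 = 0.001785 and λ₂ = 0.25 × λ₁ = 0.00044625. This gives 7.849 × 0.00223125/0.00133875² ≈ 9 771 person-years per arm. Dividing by 2 × 0.5625 = 1.125 person-years per child and doubling gives 17 371, against 17 395 printed. For the rows at 100 per 100 000, child incidence is scaled by 238/85 = 2.8.

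| Table 2 row | Printed | Recomputed |
|---|---|---|
| 100, 80% | 12 475 | 12 459 |
| 85, 80% | 14 677 | 14 657 |
| 100, 75% | 14 785 | 14 766 |
| 85, 75% | 17 395 | 17 371 |

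All four rows agree within 0.15%. For the base row, dropping the indirect effect gives 13 029 and dropping loss gives 9 771; neither fits. A log-rate formula with loss at the start of each year comes close in the 75% rows (17 432 for the base row) but misses the 80% rows (15 520 against 14 677), and it too uses both assumptions. On the basis that fits, 10 000 per arm corresponds to 17.85 × 1.125 = 20.1 control and 5.0 Vi-TCV cases.

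**Consequences at 75% efficacy.** Power ≈ Φ[(c − t)/√(c + t) − 1.96], with c control and t Vi-TCV cases; an exact conditional test is in brackets.

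- 36 and 9: 27/√45 = 4.02, power 98% (98%).
- 31.2 and 7.8: 96% (96%).
- 27.1 and 6.8: 20.3/√33.9 = 3.49, power 94% (93%).
- 23.4 and 5.9: 90% (89%).
- 20.1 and 5.0: 15.1/√25.1 = 3.01, power 85% (84%).

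Expected 95% interval for efficacy = 1 − 0.25 × exp(±1.96 × √(1/c + 1/t)). For 36 and 9 the standard error is 0.373, giving about 48% to 88%. For 27.1 and 6.8 it is 0.429, giving about 42% to 89%.

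**The case against.** The best defence is that nothing in the design rests on 36 and 9. The trial is sized from Table 2, which already contains both assumptions, and is then rounded up to 20 000. The forecast comes afterwards as description. Even on Table 2's strict basis power is 84–85%, above the 80% target. All of this stands, and it limits the severity.

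It is also fair to say that 27 and 7 is not the only possible answer. The article does not say when within each year children are lost, and with loss at year end the total is 39, only 13% below 45. That stands too, so the range belongs with the figure. It does not rescue 36 and 9, because even the most favourable timing stops at 31.2 and 7.8.

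If 36 and 9 was meant as the count before attrition, a label would make it correct. The sentence carries no such label, and a count that ignores the indirect effect but allows for loss fits equally well.

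A reader might go further in three ways that the article does not support:

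- That 20 and 5 are the cases to expect. They come from an inferred completers-only sizing convention, whereas the Data Analysis Plan counts children until they are censored.
- That the trial is underpowered or Table 2 is wrong. Neither follows from the figures above.
- That an on-plan trial would be judged short of cases. The article describes no monitoring of case accrual and no event-driven stopping; follow-up is a fixed two years, and the monitoring board's recommendations are based on safety data.

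**Conclusion.** The forecast is wrong as written: its own listed inputs contradict it under every timing of loss. With all of them applied, about 27 control and 7 Vi-TCV cases are expected, about 34 in total, which is about a quarter fewer than 45. Put the other way, 36 overstates the control count by about a third (36/27.1 = 1.33).

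The figure of 27 and 7 rests on two assumptions: loss spread through each year, and an indirect effect acting equally in both arms. The second is also what Table 2 needs in order to reproduce. Which assumption was omitted from the printed figure cannot be settled from the article.

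Severity is moderate. The stated information and precision are too favourable, but enrolment, endpoint and analysis are unaffected.

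**What to change.** Restate the forecast as about 27 control and 7 Vi-TCV cases (about 34 in total). Say that loss is taken as spread through each year, that children contribute person-time until they are lost, and that the indirect effect applies to both arms. Give the range by timing of loss (about 23 to 31 control, 6 to 8 Vi-TCV). Add the power at 20 000 (about 94%) and the expected 95% interval for efficacy (about 42–89%), both at 75% efficacy.

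Add a note that Table 2 counts only two-year completers, about 1.125 person-years per child, and that 20 000 gives about 85% power on that basis. The sponsor should confirm this convention, since it is inferred from reproducing the table.

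The cost is a rewritten sentence and a note. Enrolment does not change; the stated event count and precision become less favourable.

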### Data Analysis Plan

The incidence of typhoid will be estimated as the number of cases, divided by the total number of person-years of follow-up. The incidences will be presented with 95% CIs for each group and overall. An incidence rate ratio (IRR) will be computed as the ratio of the incidence in the Vi-TCV arm, compared to the MenA control arm. Vaccine efficacy will be calculated as (1–IRR) × 100%.

The cumulative incidence of typhoid will be summarized using the Kaplan-Meier method. Participants will be censored in the analysis at the time of their last-known residence in or near the surveillance area, at the last known contact time, or at the 2-year final visit. Statistical significance will be determined as a *P* value from a log-rank test of less than .05.

Subgroup analyses will include:

Age: <5 years and ≥5 yearsAge: <2 years and ≥2 yearsSex: male and female

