## METHODS AND ANALYSIS

### Study Design

This is a participant- and observer-blind, individually randomized, controlled trial with a 2-year follow-up to assess the protective impact of Vi-TCV.

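### Randomisation is stratified by age, but the primary rate ratio is crude and the log-rank test names no strata: valid as written, with a small, free improvement available

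*Protocol article*

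**What the plan says.** Intervention and Randomization sets 1:1 allocation "using stratified block randomization with randomly varying block sizes from 6–12". It names one stratification factor: "Stratification will be by age (9 months to <5 years old or ≥5 years old to <16 years".

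The Data Analysis Plan does not carry that factor into the primary analysis. Incidence is the "number of cases, divided by the total number of person-years of follow-up". For the effect measure, "An incidence rate ratio (IRR) will be computed as the ratio of the incidence in the Vi-TCV arm, compared to the MenA control arm", and VE is one minus that ratio. Significance rests on a P "value from a log-rank test of less than .05". The two age groups appear in this section only as a subgroup analysis.

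The two parts differ in how firmly they are stated. The rate ratio is given as a formula without an age term, so a crude estimate is what the article defines. The log-rank test is named without saying whether it is stratified.

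**The concern.** When randomisation is stratified, the usual default is to analyse by the same strata. Here the strata are age groups, and Sample Size says that age-specific incidence rates were worked out, so age was considered in relation to typhoid risk. The same section assumes that 25% of children are lost each year.

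Blocks within age strata balance age at entry, but they cannot guarantee that the age mix of the person-time stays balanced. If children of one age group left one arm faster than the other, the crude rates would average over different age mixes in the two arms. The ratio would then move away from the true effect. At stake is the accuracy of the headline VE, and to a much smaller degree the size of the test.

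**Working it through.** **Inputs from the article.** Control incidence: "with 238 cases per 100 000 people per year in children under 16 years". Vaccine effect 75%, loss 25% per year, 10 000 children per arm, two years of follow-up, and "80% Power, 5% Alpha".

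**Inputs assumed, because the article does not give them.** Share under 5 of 30%, 33% or 50%. Incidence ratio between the age groups of 2 to 4 in either direction. Yearly loss of 10% to 40%. Loss is treated as exponential and the vaccine effect as the same in both age groups.

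**Step 1: reproduce the article's expected cases.** With yearly loss l, two-year person-time per child is T(l) = (1 − (1 − l)²) / (−ln(1 − l)). For l = 0.25, T = 0.4375 / 0.2877 = 1.521 years. Control cases: 10 000 × 0.00238 × 1.521 = 36.2. Vi-TCV cases: 36.2 × 0.25 = 9.0. The article gives 36 and 9 (reproduced without the indirect effect).

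**Step 2: loss differs by age but not by arm.** Let λₐ be the control rate and Tₐ the person-time in age group a, with Tₐ equal in the two arms, and let θ be the true rate ratio. Then crude IRR = (Σ θλₐTₐ / ΣTₐ) / (Σ λₐTₐ / ΣTₐ) = θ. There is no bias, however strongly loss depends on age.

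**Step 3: loss differs by arm within an age group.** Let s be the under-5 share of an arm's person-time and r the incidence in under-5s relative to older children. The arm's crude rate is proportional to 1 + (r − 1)s, so crude IRR = θ × [1 + (r − 1)s₁] / [1 + (r − 1)s₀], where 1 is Vi-TCV and 0 is control.

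One case in full: 33% under 5, r = 3, under-5 loss 30% (control) and 20% (Vi-TCV), and loss of 25% in older children in both arms.
- T(0.30) = 1.430, T(0.20) = 1.613, T(0.25) = 1.521.
- s₀ = 0.33 × 1.430 / (0.33 × 1.430 + 0.67 × 1.521) = 0.3165.
- s₁ = 0.33 × 1.613 / (0.33 × 1.613 + 0.67 × 1.521) = 0.3432.
- Ratio = (1 + 2 × 0.3432) / (1 + 2 × 0.3165) = 1.686 / 1.633 = 1.033.
- Crude VE is −3.3% when the truth is 0%, and 1 − 0.25 × 1.033 = 74.2% when the truth is 75%.

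| Incidence, <5 : ≥5 | Yearly loss in <5, control / Vi-TCV | Crude VE, true 0% | Crude VE, true 75% |
|---|---|---|---|
| either | 25% / 25% | 0.0% | 75.0% |
| 1 : 3 | 30% / 20% | +2.3% | 75.6% |
| 3 : 1 | 30% / 20% | −3.3% | 74.2% |
| 1 : 3 | 40% / 15% | +5.6% | 76.4% |
| 3 : 1 | 40% / 15% | −8.6% | 72.9% |

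With half the children under 5, the 40% / 15% rows give 73.0% to 76.8% for a true 75%.

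The Mantel-Haenszel ratio is Σ(d₁ₐT₀ₐ/Tₐ) / Σ(d₀ₐT₁ₐ/Tₐ), where d is the number of cases and Tₐ now the total person-time of both arms in age group a. Putting in d₁ₐ = θλₐT₁ₐ and d₀ₐ = λₐT₀ₐ gives θ exactly, so every row returns 0% and 75.0%.

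**Step 4: a second pattern.** Take a 30:70 age split, incidence four times higher in older children, and 15% less person-time in older Vi-TCV children only. The null IRR is [(0.3 + 0.7 × 0.85 × 4) / 0.895] / 3.1 = 0.966, and a true VE of 75% reads 1 − 0.25 × 0.966 = 75.9%. With a twofold incidence ratio, the null IRR is 0.979.

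**Step 5: size against sampling error.** With 36 and 9 cases, the SE of ln(IRR) is √(1/36 + 1/9) = 0.37. The shift ln(0.966) = −0.035 is under one tenth of that.

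**Step 6: type I error and power.** Trials of 20 000 children were simulated, 2 000 runs per scenario, with loss shared by the arms. Loss by age was 40% / 15% or 10% / 40% (<5 / ≥5), with a threefold incidence difference. Type I error was 0.048–0.056 with either test and power 0.988–0.994 with either. Mean IRRs agreed within 0.0001, and the largest difference in z was 0.076. A separate simulation with the control rate cut by the 25% indirect effect gave 95.8% power both ways.

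Arm-specific loss was not simulated. A normal approximation with 36 cases per arm under the null (SE = √(2/36) = 0.236) gives a shift of ln(1.033)/0.236 = 0.14 SE and a type I error of about 5.2% for the 30% / 20% case. For the 40% / 15% extreme it gives ln(1.0855)/0.236 = 0.35 SE and about 6.4%.

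**The case against.** The case against raising this is strong in several respects.

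- **Nothing is contradicted.** A condensed article may leave the strata of a log-rank test to the full protocol or analysis plan. This stands for the test. It stands less well for the rate ratio, whose formula the article states without an age term.
- **A crude ratio is a valid estimator in a 1:1 trial.** This stands. A reader might infer that the plan ignores its design in a way that invalidates it, or that age-related loss alone would distort the result. Steps 2 and 6 show neither.
- **Loss that differs by arm is unlikely.** The article says "This is a participant- and observer-blind, individually randomized, controlled trial with a 2-year follow-up", keeps unblinded staff out of follow-up contacts, and attributes loss to families moving away. This stands. The pattern in Step 4 needs roughly 38% yearly loss in older Vi-TCV children against 25% in every other group.
- **Age is already examined.** The planned subgroups include the exact randomisation strata, so a marked imbalance could be noticed. That helps to detect a problem but does not correct the primary estimate.
- **Stratifying would not do everything.** A reader might infer that it makes the P value and the VE interval agree. It does not: a log-rank P value and a Mantel-Haenszel, Poisson or Cox interval are still different methods, and the article names no interval method for VE to compare. Two broad age groups also leave untouched any imbalance within a group, or loss linked to typhoid risk.

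**Conclusion.** The point holds at low severity. The design stratifies by age; the primary effect measure as defined does not, and the test is named without strata. The crude analysis is sound as long as loss is similar in the two arms, whatever its relation to age. Loss that differs by arm within an age group would move a 75% VE by less than 1 point in the 30% / 20% scenarios and by about 1 to 2 points in the 40% / 15% scenarios. Type I error and power are not materially affected, apart from a rough 6.4% in place of 5% at that assumed extreme. No likely conclusion of the trial would change.

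These sizes rest on assumed age mix, age-specific incidence and arm-specific loss, and on a common vaccine effect across age. Nothing in the article suggests that arm-specific loss is expected. The reason to act is that the stratified estimate matches the crude one when all is well and removes the between-group part of the bias when it is not.

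**What to change.** In the Data Analysis Plan, state three things:

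1. The primary VE and its 95% CI come from a rate ratio stratified by the randomisation age groups (<5 and ≥5 years), for example Mantel-Haenszel, or a Poisson or Cox model with the age stratum.
2. The primary P value comes from the log-rank test stratified by the same two groups.
3. The crude incidences and their ratio are reported as descriptive.

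If a fuller protocol or analysis plan already says this, the definition in the article need only be brought into line with it. The cost is a sentence or two: the stratum is recorded for every child at randomisation, and the simulations show no loss of power. If VE differed by age, the stratified ratio would be a weighted average across the two groups, and the planned age subgroups already allow for that to be seen.

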## OTHER ETHICS CONSIDERATIONS

All efforts will be made to conduct the research in a way that is sensitive to the Nepali culture and social values. Nepali trial staff will take consent, and the participant study-related materials (information sheet, consent forms, etc) will be printed in Nepali.

The MenA vaccine was selected as the control vaccine to ensure that the control group is receiving a beneficial intervention. The control vaccine will provide protection against group A meningitis, which is currently the most common capsular group in Nepal and can cause severe disease.

Both the intervention and control vaccines have been tested for safety in previous trials, are licenced for use in Nepal, and have received WHO prequalification. At the end of the trial, after unblinding, all participants will be offered the vaccine to which they were not randomized, allowing all participants to be vaccinated against both typhoid and meningococcal A.

For assays and analyses that are not available in Nepal, samples and data collected will be shared with other researchers in institutions outside of the country. Only anonymized samples and data will be sent outside of the research site. At the end of the study, all remaining samples in Nepal will be kept for storage in the Patan Hospital Microbiology Laboratory, as required by the Nepal Health Research Council. All samples will be kept for a minimum of 10 years after the end of the trial. These samples may facilitate important future research without needing new samples from Nepali children, should better tests become available.

Potential participants or their parents/legal guardians will be notified that they may refuse to have the relevant biological samples stored, without this influencing their study participation or the clinical care of their child. They will be informed that they may request that their samples be destroyed at any time, for any reason.

For the duration of the trial, the trial will cover the costs of standard care treatment for those participants presenting with fever ≥2 days, including the cost of tests, prescribed medications, and in-patient hospital care, as medically necessary. Incentives will be provided to children for all blood draws, in the form of school supplies.

The trial staff will ensure the maintenance of participants’ anonymity. Participants will be identified only by a participant ID number on all trial documents and electronic databases. All documents will be stored securely and will only be accessible by trial staff and authorized personnel. The trial will comply with the UK Data Protection Act, which requires data to be anonymized as soon as it is practical to do so, and with local regulations.

An independent Data and Safety Monitoring Board (DSMB) will be convened to act in an advisory capacity to the University of Oxford to monitor participant safety and data quality and to evaluate the progress of the trial. The DSMB will make recommendations to the University of Oxford about the continuation, modification, or termination of the trial, based on safety data shared with the members of the DSMB.

The protocol and all related trial materials have been approved by both the ethics committees and institutional review boards at the University of Oxford Tropical Research Ethics Committee (Oxford, UK) and the Nepal Health and Research Council (Kathmandu, Nepal).

